### Benefits, burden and safety

Women in labour will not be able to participate in the study if both birthing rooms required for randomisation are not available. Women with a preference for a particular birthing room will have only a 50% chance of being randomised to it. However, women do not usually get to choose their birthing room. In any case, women will receive midwifery and medical care according to hospital standards. Her partner or companion can be involved in supporting the woman in any birthing room.

There are indications of *benefits* for pregnant women assigned to the *intervention group*:- The intervention is in accordance with women’s desire for a more home-like environment for their birth. It offers options for various body positions and to move around, allows them to relax and may improve their well-being.- There is evidence that greater mobility and longer periods of being upright in labour result in a significantly decreased probability of episiotomy and epidural analgesia.- There is evidence that a VB will result in significantly improved client-centred outcomes, such as maternal satisfaction.

The following *burdens* might be experienced on being assigned to the *intervention group*:- Continuous foetal heart monitoring may be difficult to achieve in various positions, even if telemetry is used. If necessary, the beanbag, a chair or the mattress could be used for intermittent monitoring or auscultation.

The necessary equipment for women and newborns will be readily available in the event of an emergency. If foetal scalp blood sampling or an OVB become necessary, the screen or curtain can be removed from the birthing bed or the delivery bed can be wheeled into the room.

All AEs and SAEs will be documented in the CRF and validated in 100% of cases, including third- and fourth-degree perineal tears, blood loss >1000 ml, the composite indicator newborn health, serious maternal morbidity (e.g. amniotic fluid embolism) and serious obstetric complications (e.g. shoulder dystocia).

Participants face few foreseeable risks from the intervention. However, to ensure client safety, the following measures are planned. KKS Halle will forward the frequencies of AEs and SAEs at three points during recruitment (when 25%, 50% and 75% of the total sample have been recruited) to the independent data and safety monitoring board (DSMB). This list will detail the incidence *per OU* for the two comparison groups without revealing the identity of the study groups. The DSMB will also compare incidence with national and regional prevalence, and decide on appropriate measures. This process will be documented in writing.

### Involvement of users

Five women’s advocates – representatives from the (i) Federal Initiative to Safeguard Mother and Child during Pregnancy, Birth, and First Year of Life (Mother Hood e.V.), (ii) the Society for Antenatal Preparation, Family Education and Women’s Health (GfG e.V.), (iii) Doulas in Germany (Doulas in Deutschland e.V.) and the (iv) Association of Women’s Health in Medicine, Psychotherapy and Society (AKF e.V.) – have been involved in the preparation of the study. Their role has been to represent the views and concerns of women in labour [53]. They have been consulted on decisions concerning recruitment material, alternative designs of the birthing room, and the participant information sheet and informed consent forms. Two advocates also serve as members of the advisory board. They will receive an allowance to cover their expenses and travel costs, in recognition of their involvement and to maintain their commitment.

### Trial oversight

An independent quality management auditor (QMA-TÜV) will audit the compliance of the OUs with the study protocol in pre-trial visits as required by the funding agency (the Federal Ministry of Education and Research, or BMBF). The auditor, [name], is a midwife and research fellow of the University of Applied Sciences, Osnabrück, Germany.

The advisory board has seven members with various backgrounds from Germany and Canada: academic education and research in midwifery, obstetrical clinical practice in hospitals and two women’s advocates. They will advise the study team on challenges and solutions.

The DSMB consists of five professionals from universities in Germany and New Zealand: two clinician/researchers, two researchers (both in midwifery, obstetrics and health care), and one social psychologist with special expertise in statistics. They are independent of the trial team, funding agency and sponsor. At three points in time (when 25%, 50% and 75% of the total sample have been recruited), they will review the rates of AEs and SAEs. The DSMB can discontinue the trial if (after de-blinding) there is a decidedly higher incidence of SAEs (compared with international and national averages) in the intervention group.

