### Participants and eligibility criteria

To be adequately powered, the RCT requires a sample of (about) 3800 women (see Section 2.9). Primiparae and multiparae of all ages with a singleton pregnancy in cephalic presentation, between 37 + 0 weeks to 41 + 6 weeks pregnant on admission to the OU, in active first stage and intending to have a VB are eligible to participate in the study. Pregnant minors will be included if their legal guardian agrees with their participation.

Pregnant women will be *excluded* if they are in the active second stage, want a water birth or have limited ability to understand essential oral and written information about the trial. Women will also be excluded if an evidence-based risk exists for the woman or her baby, i.e. pathological cardiotocography on admission (based on the International Federation of Gynaecology and Obstetrics’s FIGO score), if it is an emergency admission or if there is an indication for CS according to the clinical guidelines of the UK’s National Institute for Health and Care Excellence [39]. The latter includes minor or major placenta praevia, previously diagnosed morbidly adherent placenta, women with human immunodeficiency virus (HIV; under certain conditions), and women with primary genital herpes simplex virus infection occurring in the third trimester of pregnancy.

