### Data analysis

Characteristics of the OUs (centres), study participants and outcomes are described separately for the intervention and control groups (depending on their distribution) using frequency tables, estimated probabilities, 95% CI, means ± standard deviations and percentiles. The analysis performed is intention to treat. In the primary analysis, the probabilities of a VB in the intervention and control groups are compared by Fisher’s exact test using a significance level of 5%. The risk difference and 95% CI are estimated. Additionally, randomised women with missing data in the primary outcome (e.g. dropouts) will be compared to the analysis set with respect to available characteristics, including statistical tests depending on their distribution (Fisher’s test, *t*-test or Wilcoxon rank sum test).

Sensitivity analyses for missing values will be performed in the full intention-to-treat population by multiple imputation, including adjustment for centre effects using logistic regression models with dependent variable VB (yes/no), random effects centre and intervention (versus control) as independent variable (reference for generalised linear mixed models [48]). A further logistic regression model will include an additional random effect of the interaction centre*intervention to adjust for possible centre effects on the intervention effect.

The following variables will be classified and included as independent variables in the logistic regression models above (with and without interaction with intervention) to investigate the role of potential clinically relevant prognostic factors which include: annual baseline rates of VBs of participating OU, age, body mass index, parity, induction of labour with allopathic medicine on admission to birthing room and fear of childbirth.

Five binary, log-normally and ordinally distributed *secondary outcomes* will be compared between the intervention and control groups by Fisher’s test, *t*-test (after a log-transformation if necessary) and Wilcoxon’s test. Multiple testing (five tests) will be adjusted by the Bonferroni method using a reduced significance level of 1%. No imputation is planned for the secondary outcomes.

All tests are two-sided unless otherwise stated. No interim analyses are planned, with the exception of a descriptive analysis to ensure safety (Section 2.11).

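### The only written ground for stopping the trial on safety compares intervention-arm SAEs with external averages and leaves out the concurrent randomised controls

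*Protocol article*

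**What the plan says.** Two sections of the protocol article describe safety monitoring.

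- **Trial oversight.** The DSMB reviews adverse event and SAE rates "when 25%, 50% and 75% of the total sample have been recruited". After de-blinding, it may discontinue the trial for "a decidedly higher incidence of SAEs (compared with international and national averages) in the intervention group". No other ground for discontinuation is stated.
- **Benefits, burden and safety.** At the same three points the coordination centre (KKS Halle) sends the DSMB event frequencies per OU "for the two comparison groups without revealing the identity of the study groups". The section continues: "The DSMB will also compare incidence with national and regional prevalence, and decide on appropriate measures". It also has all AEs and SAEs recorded in the case report form and validated in every case.

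Three further statements bear on the point.

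- **Participants and eligibility criteria** admits women "with a singleton pregnancy in cephalic presentation, between 37 + 0 weeks to 41 + 6 weeks pregnant" who are in active first stage and intend a vaginal birth. It adds: "Women will also be excluded if an evidence-based risk exists for the woman or her baby".
- **Data analysis** states: "No interim analyses are planned, with the exception of a descriptive analysis to ensure safety".
- **Statistical issues and sample size** sets the total at 3800 women. **Randomisation** sets allocation at 1:1.

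**The concern.** Randomisation gives the trial a comparison in which case mix, definitions and event recording are the same in both arms. The written discontinuation criterion does not use it. It sets one arm against averages from outside the trial, where all three may differ.

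The two arms then tell the DSMB something that the criterion does not ask about. If the trial's background SAE rate is below the external average, the intervention could raise it to that average and the criterion would show nothing. If the background rate is above the average, for example because every event is validated, both arms would look high and an intervention with no effect could be flagged.

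The two sections also disagree on the external reference: national and regional in one, international and national in the other. What is at stake is participant safety and the risk of an unwarranted stop.

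**Working it through.** **What the plan quantifies.** The article gives no SAE rate and no number for the discontinuation criterion, so there is no figure of its own to reproduce. All SAE rates below are assumptions.

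**Women per arm at each review** (3800 women, 1:1):

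- 25%: 0.25 × 3800 / 2 = 475
- 50%: 0.50 × 3800 / 2 = 950
- 75%: 0.75 × 3800 / 2 = 1425

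**Example 1: a doubling that the benchmark hides.** Assume controls 1%, intervention 2%, external average 2%.

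- Against the benchmark: 2% − 2% = 0 at every review.
- Against controls: z = (q − p) / √(2·p̄·(1 − p̄)/n), with p = 0.01, q = 0.02, p̄ = 0.015. The numerator is 0.01, and 2 × 0.015 × 0.985 = 0.02955.

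| Review | n per arm | √(0.02955/n) | z |
|---|---|---|---|
| 25% | 475 | 0.00789 | 1.27 |
| 50% | 950 | 0.00558 | 1.79 |
| 75% | 1425 | 0.00455 | 2.20 |

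Only the 75% review exceeds 1.96.

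**Example 2: a range of assumed rates.** To compare the two yardsticks on equal terms, a one-sided nominal 2.5% level was used for both: an exact binomial test of the intervention arm against a fixed external rate, and Fisher's exact test against controls. That level is a device for the comparison. It is not in the article and is not proposed. Entries are the probability of a signal at 475 / 950 / 1425 women per arm.

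True doubling, with the intervention arm at the external average:

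| External | Controls | Intervention | Against external | Against controls |
|---|---|---|---|---|
| 2% | 1% | 2% | 1.7 / 1.8 / 2.3% | 17 / 36 / 54% |
| 3% | 1.5% | 3% | 1.8 / 2.2 / 2.0% | 28 / 54 / 74% |
| 5% | 2.5% | 5% | 2.5 / 2.2 / 2.1% | 47 / 80 / 93% |

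No effect, with both arms at 1.5 times the external average:

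| External | Both arms | Against external | Against controls |
|---|---|---|---|
| 3% | 4.5% | 39 / 69 / 83% | about 2% |
| 5% | 7.5% | 64 / 89 / 97% | about 2% |

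**When the yardsticks agree.** If the trial's background rate equals the external rate, the external comparison gives about 2% false signals at each review, which is acceptable. The problem depends on a mismatch. The article gives no ground for assuming equality, and its eligibility criteria and full validation of events are grounds for doubting it.

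**The case against.** The strongest reply is that this reads a summary sentence as a binding rule. The DSMB receives both masked groups. The word *also* in Benefits, burden and safety presents the external comparison as an addition to a between-group look, and the mention of de-blinding in Trial oversight fits that order. The verb is permissive, and the same section leaves the DSMB to decide on measures. Detailed rules commonly sit in a charter that is not shown. This stands in part: the DSMB has the contrast and its discretion, and the lack of a numeric boundary is no finding. It does not remove the point, because the article does name a comparator for discontinuation and that comparator is external.

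Second, the sizes rest on assumed rates and, in Example 2, on an assumed test level. This stands. In Example 1 the control comparison is itself weak at the first two reviews. With matched rates a fixed benchmark is even the more sensitive yardstick.

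Some stronger readings are tempting, but the documents do not support them.

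- **That the averages cover births of every risk level.** The article does not say which population they cover. Mode of birth quotes national figures restricted to term singleton cephalic births, and the newborn composite is a national indicator for term infants.
- **That events confined to vaginal birth would be inflated by 9 to 16% without any harm.** This divides 74% and 79% by 67.9% (100 − 32.1% caesareans among all births). The like-for-like national rate in Mode of birth is 75.2%, giving 0.74/0.752 = 0.98 and 0.79/0.752 = 1.05. Moreover, 79% is the rate under the hoped-for benefit, so it cannot illustrate an absence of effect.
- **That listing incidence per OU hides the overall picture.** Nothing prevents adding the 12 units together within each masked group.

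**Conclusion.** The point holds as a defect in the written criterion. The only stated ground for discontinuation omits the concurrent controls, and the two safety sections name different external references. Followed as written, the criterion can miss a real excess or flag a harmless one.

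The size depends on how far trial and external rates differ, which the article does not let one determine. Where the trial's background rate is half the external average, a doubling signals about 2% of the time against the benchmark, compared with 17% to 93% against controls over the assumed rates and the three reviews. Where the background rate is 1.5 times the average, an intervention with no effect is flagged 39% to 97% of the time against the benchmark, compared with about 2% against controls.

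A reader might infer that the DSMB cannot see the randomised contrast, or that the control arm would expose harm at every review. Neither follows: both groups are supplied, and at 1% versus 2% z is only about 1.3 and 1.8 at the first two reviews. The primary efficacy analysis is not affected.

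**What to change.** Reconcile Trial oversight with Benefits, burden and safety, in the protocol and in any DSMB charter:

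- Name the comparison of the intervention arm with the concurrent randomised control arm as the basis of the discontinuation criterion. Present it at the 25%, 50% and 75% reviews as a difference pooled over OUs and stratified by OU, with a confidence interval.
- Choose one consistent set of external figures (regional, national or international), state which births they cover, and keep them as context.
- Keep the per-OU listings as context too.

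No numeric threshold is proposed, and the DSMB's discretion stays as it is. The cost is about one sentence of text and one extra table per review, from data and allocation codes that KKS Halle already holds.

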## Discussion

This trial is of interest to service users, providers of maternity care, heads of service, academics and researchers. Therefore, the trial and its results will be reported in international peer-reviewed journals, national midwifery and obstetric journals, regional newspapers, and at national and international conferences.

If the intervention proves effective, it can be translated into routine practice at a modest cost and minimal burden to staff. Moreover, nationwide implementation could allow an additional 21,000 women per year to experience a VB instead of a CS. Other expected benefits for women in labour and mothers are increased self-determination during labour, fewer medical interventions, improved client-centred outcomes, fewer CSs in subsequent pregnancies and possibly lower health-care costs.

### Trial status

The RCT was registered with the German Clinical Trials Register (*Deutsches Register Klinischer Studien*) on 7 March 2018, registration number DRKS00012854. The assigned universal trial number is U1111–1204-0964. Additional file 2 lists all items from the World Health Organization Trial Registration Data Set. This protocol is based on version 4 of 7 June 2018. Recruitment of study participants started on 2 April 2018 and will continue until February 2020.

## Abbreviations

AE: Adverse event
BE-UP: Birth environment, upright position
CI: Confidence interval
CRF: Case report form
CS: Caesarean section
DSMB: Data and safety monitoring board
HELLP: Hemolysis, elevated liver enzymes, and a low platelet count
KKS: Coordination Centre for Clinical Trials
OU: Obstetric unit
OVB: Operative vaginal birth
RCT: Randomised controlled trial
RR: Relative risk or risk ratio
SAE: Serious adverse event
VB: Vaginal birth
